## Abstract

**Background:**

As the population of Korea ages, interest in healthcare has increased. In particular, there is an increasing demand for immune-function improvement to prevent infectious diseases. *Phellinus linteus* (PL) has previously been shown to exert immune-enhancing and anticancer effects. We aim to evaluate whether PL mycelium extract, cultured from the PL KCTC0399BP strain, can increase immune function, as measured using blood-test indicators. This clinical trial protocol is designed as the main trial and is based on the results of a pilot study.

**Methods:**

This clinical trial is a randomized, double-blinded, placebo-controlled trial. Ninety-eight participants are enrolled and randomly divided into two groups: the experimental group (PL 1000 mg) and the control group (placebo). Participants are administered with experimental food or placebo for eight weeks. Blood tests are performed before trial initiation and 8 weeks later, at trial completion. Laboratory evaluation items are as follows: natural killer cell activity, tumor necrosis factor-α, interferon-γ, interleukin (IL)-1β, IL-2, IL-6, IL-12, immunoglobulin (Ig)G1, IgG2, and IgM. We will mainly use the full analysis dataset to statistically analyze the effectiveness of the treatment.

**Discussion:**

This study evaluates the effects of PL extract on immune function and will contribute to knowledge on the value of PL as an immune-function–boosting functional food.

**Trial registration:**

Clinical Research Information Service (CRIS) of Korea CRIS-KCT0005460. Registered on 12 October 2020

## Introduction

There is global, growing interest in human health, and the demand for medicines and foods that boost immune function is increasing with the advent of aging populations and the spread of infectious diseases [1]. Immunity is a means of defense that protects our bodies from external influences. From mild diseases such as colds to infectious diseases and cancer, immunity is a key factor.

*Phellinus linteus* (PL) has established immune-improving functions, and it has been reported to increase the activity of interleukin (IL)-12, interferon (IFN)-γ, and natural killer (NK) cells [2, 3]. In previous studies, it has been reported that PL extract increases immunity, mediated by cells such as T lymphocytes, NK cells, macrophages, and B lymphocytes [4], and exhibits antitumor and antioxidant activities [5].

In a patent for an extract produced using the existing PL KCCM KSSW01 strain, the immunity-enhancing effect of the glucomannan in the extract was proven [6]. Glucomannan consists of 53.7% glucose, 23.5% mannose, 7.7% galactose, 7.1% xylose, 5.8% fructose, and 2.2% 3-O-methylglucose. The PL extract used in the present study, which was produced using the PL KCTC0399BP strain, contains galactomannoglucan. Galactomannoglucan comprises 78.6% glucose, 18.0% mannose, and 3.4% galactose and is thus quite different from glucomannan [7].

The PL extract used in this clinical trial is marketed as Mesima, an immunostimulant, in the Republic of Korea. This clinical trial aims to analyze and evaluate whether this PL extract, when used as an ingredient of a functional health food, can effectively improve immune function. We evaluate changes in (1) NK cell activity and (2) cytokines (white blood cells [WBC]; tumor necrosis factor [TNF]-α; IFN-γ; immunoglobulin [Ig]G1, IgG2, and IgM; and IL-1β, IL-2, IL-6, and IL-12) to verify the efficacy of the PL extract in preventing immunity weakening. This clinical trial is the main trial, and it is designed to confirm efficacy and stability based on the results of a pilot study.

## Methods

### Study design

This is a prospective, double-blind, single-center, randomized, controlled clinical trial designed to demonstrate the effects of PL extract on immune function. Recruitment starts in October 2020 and the trial ends in March 2021. Subjects are recruited via placards on outdoor billboards and banners in Daejeon University Cheonan Korean Medicine Hospital. All subjects receive written explanations and informed consent forms for the clinical trial protocol from a Korean medical doctor (KMD). The KMD also comprehensively explains the study to the recruited subjects, receives informed consent from them, and selects participants in the study based on detailed screening.

The study planned to recruit 98 subjects who will be randomly assigned in a 1:1 ratio to either the experimental group (PL 1000 mg) or the control group (placebo). The subjects take one 500 mg capsule twice daily for eight weeks, and this capsule contains either PL or dextrin, depending on the group they had been assigned to.

The variables we evaluated are NK cell activity, TNF-α, IFN-γ, IL-1β, IL-2, IL-6, IL-12, IgG1, IgG2, and IgM. Blood samples are taken for this laboratory test on the first day of participation, before the subjects has begun ingesting the test food, and 8 weeks later, at the end of the trial. The subjects visit the clinic three times and the clinical trial span a total of eight weeks (Table 1, Fig. 1).

**Table 1 Tab1:** Clinical trial process for the *Phellinus linteus* extract clinical trial protocol

Section	Screening	Visit 1 (baseline visit)	Visit 2 (during trial)	Visit 3 (trial end)
	(− 2 weeks to 0 days)	(0 days)	(4 weeks ± 5 days)	(8 weeks ± 5 days)
Prepare a written consent form	√			
Evaluate inclusion/exclusion criteria	√			
Examine subject information	√			
Assign screening number	√			
Assign random numbers to subjects		√		
Investigate medical history and medication history	√	√		
Conduct physical examination	√	√	√	√
Assess vital signs	√	√	√	√
Conduct clinical laboratory blood test	√	√		√
Conduct pregnancy test	√			
Observe upper respiratory tract infection symptoms		√	√	√
Distribute experimental/control foods		√	√	
Measure effectiveness-evaluation variables		√		√
Check adverse events			√	√
Identify concomitant drugs			√	√
Check compliance			√	√
Confirm cancelation and withdrawal criteria		√	√	√

**Fig. 1 Fig1:**
[figure not shown]
SPIRIT checklist showing the schedule of enrollment, assessments, and allocation for each subject in the *Phellinus linteus* extract clinical trial protocol

### Inclusion and exclusion criteria

The inclusion criteria are as follows: (1) age of 20–65 years, (2) peripheral white blood cell count of 3–10 × 10^3^/μL, (3) upper respiratory tract infection or symptoms of a common cold at least twice within the year preceding the beginning of the trial, and (4) agreement to participate in this trial and voluntary signing of a written informed consent form (by the subject or a legal representative).

The exclusion criteria are as follows: (1) currently being treated for a clinically significant acute or chronic cardiocerebrovascular, immune, respiratory, hepatobiliary, kidney, urinary, nervous, musculoskeletal, psychotic, infectious, or hematologic/neoplastic disease (however, it was possible to participate in the study at the discretion of investigator who evaluated the subjects); (2) uncontrolled hypertension (160/100 mmHg or more, measured after 10 min of rest); (3) uncontrolled diabetes (fasting blood glucose ≥ 126 mg/dL, or commencement of a new drug to treat diabetes within the previous 3 months); (4) aspartate aminotransferase (AST) (glutamic-oxaloacetic transaminase [GOT]) or alanine aminotransferase (ALT) (glutamic-pyruvic transaminase [GPT]) blood level ≥ 3 × the normal upper limit of the institution; (5) creatinine blood levels > 2.4 mg/dL in males and > 1.8 mg/dL in females; (6) ingestion of nutritional supplements, which can affect immunity, within 2 weeks before the screening; (7) severe gastrointestinal symptoms, such as heartburn or indigestion; (8) pregnancy, lactation, or an intention to fall pregnant during the study period; (9) sensitivity or allergy to foods related to the test food; (10) concurrent participation in other studies; (11) ingestion of other experimental drugs within four weeks of starting this study; and (12) unsuitability for this study (as determined by the investigator) based on overall health status.

### Dosage calculation

A dose of 200 mg/kg administered to mice for 1 week did not exhibit any specific toxicity. This effective dose was converted to a human intake dose of 960 mg/d (16 mg/kg/day), based on an adult body weight of 60 kg and a conversion factor of 0.08, which takes the relationship of body weight to body surface area into account. In a preliminary clinical study in which PL extract was ingested at 1000 or 2000 mg/day, no related adverse reactions were observed, and it was confirmed that immune function improved at 1000 mg/day. Therefore, the PL extract intake is set to 1000 mg/day for this study, based on the results of these preliminary clinical and animal studies.

### Sample size calculation

The necessary sample size is calculated using the NK cell activity results from the pilot study, in which this variable is used to evaluate efficacy. Calculations are performed using G*power 3.1.9.4, and the minimum number of subjects required to confirm statistical significance is determined to be 41 individuals per group. Accounting for a dropout rate of 15%, we aim to recruit a total of 98 people, with 49 for each group.

### Randomization and blinding procedures

The final registered subjects are assigned in a 1:1 ratio to the experimental and control groups using block randomization. The size of the blocks is set as random by statisticians. The investigators are therefore blinded to the size and number of blocks used for the random assignments. The total number of random assignments is generated on a scale of approximately 120% of the target recruitment number. A three-digit randomized number is assigned to each subject and the test food or a placebo is distributed to the subjects according to this number. Both the investigators and the subjects are blinded to the subjects’ treatment group. Randomization details are generated by statisticians using nQuery Advisor 7.0 (or SAS 9.0 or SPSS 21.0). Each subject’s randomized number and group-assignment details are placed in a nonpermeable, sealed bag, which was given to the supervisor for storage and management. Once a randomized number has been assigned, it is not reused, even if the subject it is first assigned to dropped out of the study.

### Intervention

The test food is obtained from Hankookshinyak Pharmaceutical (Nonsan, Republic of Korea). The appearance and physical properties of the test food and placebo are identical: no difference could be observed with the naked eye and the weight is identical (Table 2, Fig. 2). The placebo contains 500 mg dextrin per capsule, and the test food contains the same quantity of the PL extract. In addition, the capsules are placed in identically labeled paper envelopes, to ensure that the researchers and subjects remained blinded to treatment assignments.

**Table 2 Tab2:** Ingredients of *Phellinus linteus* extract

Ingredient	Quantity/percentage
Calories (Kcal/100 g)	346.36 Kcal/100 g
Carbohydrate (%)	68.86%
Crude protein (%)	15.75%
Crude fat (%)	0.88%
Sodium (mg/100 g)	71.57 mg/100 g
Sugars (mg/g)	128.29 mg/g
Saturated fat (g/100 g)	0.07 g/100 g
Trans fat (g/100 g)	–
Cholesterol (mg/100 g)	–

**Fig. 2 Fig2:**
[figure not shown]
*Phellinus linteus* extract and placebo capsules, showing their identical appearance

The subjects ingest one capsule twice a day, 30 min after meals, for 8 weeks. The investigator collects the empty envelopes after every visit by the subjects, to verify that they had taken their treatment. Any other treatment received during their participation in the trial, functional health foods taken, or additional therapies are considered to be combination therapy. If coadministration is necessary, the administration details are recorded in the case report form (CRF) and treatment chart, and the existing therapy remained unchanged. Concomitant drug administration was minimized during trial participation, however. Concomitant drug administration is allowed based on the judgment of principal investigator, when it is deemed inconsequential to the trial. If a drug directly affected immune function, that subject withdraws from the trial.

### Outcome measures

The primary outcome is the amount of change in NK cell activity. NK cells play a key role in immune function against viruses and have recently been shown to play an important role in anticancer activity [8]. NK cell activity is measured to evaluate whether immune function increased as a result of the treatment. The secondary outcome is the amount of change in WBC in the peripheral blood and in the levels of TNF-α, IFN-γ, IL-1β, IL-2, IL-6, IL-12, IgG1, IgG2, and IgM. Proinflammatory cytokines such as TNF-α, IFN-γ, IL-1β, IL-2, IL-6, and IL-12 are factors that regulate the inflammatory responses of tissues [9]. Immunoglobulins such as IgG1, IgG2, and IgM are involved in virus neutralization and aggregation reactions. They also play a major role in immunity against influenza [10]. Changes in immune function can thus be confirmed by measuring changes in cytokines and immunoglobulins.

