### Statistical analysis

Demographic data collected during screening will be tested using *t* tests (or Wilcoxon rank–sum tests) for continuous data. For categorical data, a chi-squared test (or Fisher’s exact test) will be performed. Effectiveness evaluation will be based on the results of the full analysis dataset. The per-protocol (PP) group will also be analyzed for reference. Statistical significance will be determined based on a significance level of 5%. If the difference between the two groups is normally distributed, an independent *t* test will be performed; if not, a Mann–Whitney *U* test will be performed. To test for differences before and after the treatment within a group, paired *t* tests will be used for normally distributed data; otherwise, Wilcoxon’s signed-rank tests will be used. The Shapiro–Wilk test will be performed to test the normality of continuous variables. When a difference between groups is observed, the drinking history variable will be considered for control variable, and additional covariate analysis will be performed. In the full dataset analysis, missing values will be replaced by the last observation carried forward. For the safety evaluation, the 95% confidence interval for each group will be determined by calculating the rate of occurrence of adverse reactions, and comparisons will be made between the groups. From the results of each laboratory test, continuous data such as vital signs will be compared with the baseline and analyzed using either a *t* test or a paired *t* test. If the assumption of normality is not satisfied, the Wilcoxon signed-rank test or the Wilcoxon rank–sum test will be performed. Categorical data will be analyzed using chi-squared tests and Fisher’s exact tests to determine whether there are differences between the groups in terms of the frequency and ratio of each category.

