## Discussion

The importance of immune function is increasing with the spread of infectious diseases in modern society worldwide. The immune system comprises various cytokines, immunoglobulins, and phagocytic cells that protect the body from external intruders. Infectious diseases related to immune systems are fatal in the elderly population, which has reduced immune function. Therefore, in modern societies with aging populations, the demand for foods that improve immune function is increasing.

PL extract has an anticancer effect because it improves immune function [11]. Studies have reported the anti-inflammatory effects of PL extract in rats [12], the anti-inflammatory mechanisms of PL extract in macrophages [13], and the antioxidant and antimicrobial activities of PL extract [14]. NK cells, which are responsible for innate immunity, play important anticancer [15] and antiviral [16] roles in immune function. According to the functional health food evaluation guide distributed by the Ministry of Food and Drug Safety in the Republic of Korea, NK cell activity should be evaluated by culturing effectors and target cells together, followed by flow cytometry or lactate dehydrogenase cytotoxicity assay kits. The lactate dehydrogenase assay is a method of measuring cell death that evaluates NK cell activity by analyzing NK cell cytotoxicity [17]. In existing clinical trials, a diagnostic kit is used to measure NK cell activity. The kit artificially activates NK cells using engineered recombinant cytokines, and then measures NK cell activity via IFN-γ detection. The kit has analysis limitations because it is not possible to evaluate NK cell activity using the effector to target concentration ratio. In this clinical trial, NK cell activity is confirmed using lactate dehydrogenase assays at various concentrations of effector to target cells (e.g., 12.5:1, 25:1, and 50:1). Changes in NK cell activity, proinflammatory cytokines, and Igs will be evaluated to confirm any improvement in immune function due to the consumption of PL extract. The study aims to verify the efficacy of PL extract as a health supplement by proving its beneficial effects on immune function.

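### Cytokine and immunoglobulin changes are said to confirm improved immunity, and within-group tests are not marked supportive, so the efficacy conclusion is not tied to the randomised NK comparison

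*Protocol article*

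**What the plan says.** All references are to the protocol article.

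- **Outcome measures** sets a hierarchy: "The primary outcome is the amount of change in NK cell activity". It then lists ten secondary markers, beginning "The secondary outcome is the amount of change in WBC in the peripheral blood and in the levels of TNF-α, IFN-γ, IL-1β, IL-2, IL-6, IL-12" and ending with IgG1, IgG2 and IgM.
- **Sample size calculation** uses the pilot NK results only and arrives at 41 per group, or 49 after allowing for 15% dropout.
- **Outcome measures** closes with "Changes in immune function can thus be confirmed by measuring changes in cytokines and immunoglobulins". That sentence covers nine of the ten secondary markers (six cytokines and three immunoglobulins). White cell count is not in it.
- **Discussion** puts the markers on the same footing as the primary: "Changes in NK cell activity, proinflammatory cytokines, and Igs will be evaluated to confirm any improvement in immune function".
- **Introduction** also lists them side by side ("We evaluate changes in (1) NK cell activity and (2) cytokines") as the means of verifying efficacy.
- **Statistical analysis** gives one threshold: "Statistical significance will be determined based on a significance level of 5" per cent. The between-group test is described first ("If the difference between the two groups is normally distributed", a t test, otherwise Mann–Whitney). Paired tests follow directly: "To test for differences before and after the treatment within a group". The same section labels the per-protocol analysis as being for reference, but gives the within-group tests no such label.

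**The concern.** Naming a primary outcome protects the 5% error rate only if the efficacy conclusion is confined to it. Here the language of confirmation also covers the secondary markers, and the before/after tests sit in the effectiveness analysis with no stated status.

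The two routes fail for different reasons. Among many between-group tests at 5%, one or more can be significant by chance. A before/after test within one arm does not estimate a treatment effect at all, because anything that moves both arms moves it too. Recruitment starts in October and the trial ends in March, and subjects are selected for at least two colds or upper respiratory infections in the preceding year. A shift common to both arms is therefore plausible.

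The article says the trial is to verify the efficacy of PL as a health supplement. At stake is a report of confirmed immune improvement beside a negative randomised NK comparison.

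**Working it through.** **Inputs from the article.** One 5% level. One primary and ten secondary markers, 11 in all, with nine in the sentence that uses the word confirm. 41 evaluable subjects per arm. The enrolment figure reproduces: 41/0.85 = 48.2, rounded up to 49 per arm, and 2 × 49 = 98.

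**Assumptions, not in the article.** Tests are two-sided. NK activity counts as one reading, although the Discussion gives several effector-to-target ratios as examples. The correlation between markers and the size of any common drift are not given, so each is shown over a range.

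**Step 1: between-group tests, no treatment effect, independent markers.** The chance of at least one p<0.05 in k tests is 1 − 0.95^k.

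| Tests | k | Chance |
|---|---|---|
| Primary alone | 1 | 5% |
| Markers in the quoted sentence | 9 | 1 − 0.95^9 = 37.0% |
| All secondary markers | 10 | 1 − 0.95^10 = 40.1% |
| All markers | 11 | 1 − 0.95^11 = 43.1% |

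The case of interest is a negative NK test with at least one positive secondary: 0.95 × 0.401 = 38.1%.

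**Step 2: correlated markers.** Simulation with equal correlation between markers, 41 per arm, 4,000 runs.

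| Assumed correlation | 10 secondary markers | All 11 markers |
|---|---|---|
| 0.3 | 36% | 37% |
| 0.5 | 29% | 31% |
| 0.8 | 18% | 19% |

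If only one direction counts as favourable, the figures for the ten secondaries are 1 − 0.975^10 = 22.4% under independence, and about 18%, 15% and 9% at the three correlations.

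**Step 3: within-arm paired test, no treatment effect, a drift common to both arms.** Let the drift be δ in SD units of the change. With n = 41 the paired t statistic is noncentral t with 40 degrees of freedom and noncentrality δ√41. Let p be the probability that it exceeds the upper 2.5% point, a significant increase. The arms are independent, so PL is significant while placebo is not with probability p(1 − p).

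| δ | δ√41 | p, per marker | p(1 − p), per marker |
|---|---|---|---|
| 0 | 0 | 2.5% | 2.4% |
| 0.1 | 0.64 | 9.1% | 8.3% |
| 0.2 | 1.28 | 23.9% | 0.239 × 0.761 = 18.2% |
| 0.3 | 1.92 | 46.6% | 0.466 × 0.534 = 24.9% |

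The last column matters because PL improving significantly while placebo does not is easily read as an effect, although the true between-group difference in this calculation is zero.

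**The case against.** The strongest reply is that the article does have a hierarchy: one named primary, a sample size based on it, and a statement that NK activity is measured to see whether immune function rose as a result of treatment. The between-group test of that outcome runs at 5%. The sentence with the word confirm closes a paragraph of biological rationale and can be read as explaining why the markers are measured. All of this stands, and it limits the point.

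A reader might infer more than the documents support:

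- **That any one of 11 markers is enough for success.** No section states this. The quoted sentence covers nine markers and gives no criterion.
- **That a within-arm change is an efficacy criterion.** No section says so. The tests are simply listed without a stated status.
- **That a false claim is likely.** The between-group chance over all 11 markers is 43% under independence and about 19% at a correlation of 0.8. The within-arm figures rest on an assumed drift for which the article gives no value.
- **That a missing multiplicity adjustment, or a missing expected direction for each marker, is an error.** Both are commonly left to a statistical analysis plan, which is not shown. The Introduction does cite earlier reports of increases in IL-12 and IFN-γ.

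What the reply does not remove is the wording. An adjustment in an unseen plan would not change two sections that speak of confirming improvement from secondary markers. Nor can the silence on the within-group tests be put down to a habit of not labelling, since the same section does label the per-protocol analysis.

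**Conclusion.** The concern holds in limited form. The article names and powers a single primary outcome, but does not confine the efficacy conclusion to it. It attaches confirmatory language to cytokines and immunoglobulins, and lists within-group significance tests in the effectiveness analysis without subordinating them.

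If that wording guided the report, the chance of at least one false between-group signal among the ten secondaries would be 40% under independence and about 18% to 36% at correlations of 0.8 to 0.3, against 5% for the primary alone. Under a common drift of 0.2 to 0.3 SD, a within-arm increase on PL would be significant in 24% to 47% of trials per marker, and significant on PL but not on placebo in 18% to 25%. The correlations and the drift are assumptions. These figures show what the wording permits and do not predict what the trial will report.

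**What to change.** In Outcome measures, Statistical analysis and the Discussion:

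1. State that the efficacy conclusion rests only on the between-group comparison of change in NK cell activity.
2. Where cytokines and immunoglobulins are said to confirm improved immune function, say that they support it, and report them as between-group estimates with confidence intervals.
3. Report within-group changes descriptively, as mean change with a confidence interval, and not as significance tests of effectiveness.

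This changes wording and reporting only. The sample size, visits and assays stay as they are, and the type I error of the efficacy conclusion is 5%. The cost is that fewer secondary or within-arm results can be called significant.
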